## Abstract

**Background:**

Transcutaneous electrical nerve stimulation (TENS) has been used as analgesic therapy in many diseases. It is already known that studies that have observed the relationship between pain and cytokines have found that patients who report less severe pain have less production of proinflammatory cytokines. However, one another accepted mechanism is that decreasing proinflammatory cytokines results in decreased pain intensity. Analyzing the literature, the authors describe that, in addition to the analgesic effect, TENS has shown systemic effects, and clinically, the reduction of proinflammatory cytokines could be a protective factor against inflammation. To test the inflammatory effect of TENS, we researched the literature for clinical conditions that suggest that proinflammatory cytokines are one of the main mediators of the disease process. Chronic inflammation is one of the risk factors mentioned for the development of a new cancer; at the same time, it is indicated as an indicator of the worst prognosis. Studies also suggest that the worst prognosis of breast cancer, one of the types with the highest incidence in the world, may be related to increased inflammatory activity. Considering that inflammation is increased in breast cancer and that TENS can reduce proinflammatory cytokines even without blocking the pain pathway, our hypothesis is that the anti-inflammatory effect of TENS can bring benefits to these patients. The aim of this study will be to evaluate the effect of TENS on blood reduction of proinflammatory cytokines in breast cancer patients.

**Methods:**

This study will evaluate at least 59 patients, over 18 years of age, diagnosed with breast cancer, but who have not yet started any treatment. All patients will be submitted to TENS intervention (Ibramed, Model Neurodyn III, parameters: VIF—turn on, frequency—2-247 Hz, pulse size—50-500 *μ*s, and intensity (mA)—maximum tolerated by the patient), and the data will be analyzed in the pre- and postintervention of each patient. The application has a total duration of 30 minutes, and 8 ml of blood will be collected before and after the intervention. Proinflammatory (IL-1, IL-2, IL-6, IL-7, and TNF-*α*) and anti-inflammatory (IL-4, IL-10, IL-13, and FTC*β*) cytokines will be analyzed. As a primary endpoint, we will analyze the reduction in blood concentration of proinflammatory cytokines, and as secondary endpoints, we will analyze the size of the effect according to each type of proinflammatory cytokine, describe the effect size of the reduction according to the breast cancer immunohistochemistry, and analyze the effect of TENS on anti-inflammatory cytokines. This study is approved by the Research Ethics Committee (Centro Universitário FMABC, Brazil) and registered in the Brazilian Clinical Trials (Search text: RBR-10jbwh47).

## 1. Background

Used since 1970 as an adjunct therapy to control acute and chronic pain in a lot of medical and surgical conditions, transcutaneous electrical nerve stimulation (TENS) is a noninvasive physiotherapeutic resource that acts to block pain through the central nervous system [1–5].

After pain is present, there are two mechanisms of action that may be involved: (i) blocking nociception reduces the production of proinflammatory cytokines or (ii) decreasing proinflammatory cytokines that decrease pain intensity [6–8].

It is already known that studies that have observed the relationship between pain and cytokines have found that patients who report less intense pain have less production of proinflammatory cytokines [9, 10].

The mechanism block pain described above was thought of for the hypothesis that the TENS, a physiotherapeutic resource that acts in the path of pain, could reduce cytokines. To answer the question, a systematic review of randomized clinical trials was carried out, and it was found in the meta-analysis that TENS significantly reduced blood proinflammatory cytokines compared to the control group [11].

Analyzing the literature, the authors describe that in addition to the analgesic effect, the electric current has also shown systemic effects, and one of those that is mentioned is the anti-inflammatory effect [6, 12–15].

In the systematic review, we observed that one article evaluated the reduction of cytokines and pain [12]. The other articles evaluated the reduction of cytokines in chronic diseases such as COPD [16] and rheumatoid arthritis [16, 17] and also during surgery [18].

In the research of Wang et al. [18], for example, which evaluated outcomes during a brain surgery, the use of TENS showed a reduction in intraoperative cytokines while the control group had an increase. Considering that inhibiting the inflammatory response in the brain (reduction of proinflammatory cytokines) can minimize brain damage, treatments with TENS may improve the prognosis after surgery.

By analyzing the studies related to chronic disease [16–19], it was hypothesized that TENS could act firstly in the cytokine reduction pathway. If TENS has this effect even without pain being present, clinically the reduction of proinflammatory cytokines could be a protective factor against inflammation.

For testing the effect of TENS on cytokines without block pain, we searched the literature for clinical conditions suggesting that the proinflammatory cytokines are one of the main mediators of the disease process.

The chronic inflammatory process can be related to an increased risk to develop cancer, since it implies changes in the tissue microenvironment [20, 21]. This tissue change induces cell proliferation, promotes angiogenesis, and increases the survival of tumor cells (because it inhibits their apoptosis). That influences the migratory behavior and contributes to cellular dissemination and metastasis [22–24].

Whenever inflammatory cells secrete a variety of factors, including chemokines and cytokines [25], they further promote tumor progression instead of promoting an antitumor response [26].

The cancer immune system is related to the production of catabolic signals and stimulation of the production of proinflammatory cytokines and growth factors by tumor cells. The increase of Tumor necrosis factor alpha (TNF-α) paired increase of interleukins might be related a worst prognosis in cancer. The chronic inflammation can result in an increased possibility of developing a new cancer [27].

Several types of cancer are studied in the literature, but the relationship between chronic inflammation and cytokines was initially observed in breast cancer [20, 21, 28]. The studies suggest that the worst prognosis of breast cancer may be related to increased inflammatory activity [20, 21, 28].

Breast cancer is one of the types with the highest incidence in the world, and because of that, several topics are developed to identify potential risk factors and protection against cancer [29–31].

Considering that inflammation is increased in breast cancer and that TENS can reduce proinflammatory cytokines even without blocking the pain pathway, our hypothesis is that the anti-inflammatory effect of TENS can cause benefit for these patients. The aim of this study will be to evaluate the effect of TENS on blood reduction of proinflammatory cytokines in patients with breast cancer.

## 2. Study Rationale

TENS is a noninvasive, easy-to-apply, and low-cost therapeutic resource. Several studies have pointed out the benefits of TENS in a variety of pathologies, and, so far, no deleterious effects of the use of TENS are known.

The main clinical benefit would be that the reduction of proinflammatory cytokines (protective factor against inflammation) could be applied in diseases that have inflammatory causes or inflammatory complications. We could use TENS as a regulator of the inflammatory process.

Regarding the research risks, we can mention complications resulting from procedures such as skin irritations and a small cutaneous hematoma during blood collection.

## 3. Study Objectives and Study Design

A protocol of clinical trials was developed following the guidelines of Standard Protocol Items: Recommendations for Interventional Trials (SPIRIT) [32]. The checklist for SPIRIT can be seen in Supplementary Material 1.

The objective of this study is carried out to assess the reduction of proinflammatory cytokines after TENS application in patients with breast cancer. A nonrandomized, open, single-arm clinical trial with paired analysis will be developed. The study design is described in Figure 1.

A minimum of 59 patients is expected. All subjects will receive a single application of TENS for 30 minutes. Assessments will be made before and after application. Screening data will be reviewed to determine subject eligibility. Individuals who meet all of the inclusion criteria and none of the exclusion criteria will be included in the study. The total duration of the subject's participation will be one day (time to complete all study evaluations).

## 4. Criteria for Evaluation

The endpoints for the study are described below:

*Primary Endpoint*. The primary endpoint is to analyze the reduction in blood concentration of proinflammatory cytokines.

*Secondary Endpoint*. The secondary endpoints are to analyze the effect size according to each type of proinflammatory cytokine, describe the effect size of the reduction according to breast cancer immunohistochemistry, and analyze the effect on anti-inflammatory cytokines.

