### 7.1. Clinical Laboratory Measurements

The blood will be collected and sent to the clinical laboratory. The study's dependent variables will be the proinflammatory cytokines interleukin 7 (IL-7), interleukin 6 (IL-6), interleukin 2 (IL-2), interleukin 1 (IL-1b and IL-1*α*), and TNF alpha (TNF-*α*) and the anti-inflammatory cytokines interleukin 4 (IL-4), interleukin 4 (IL-10), interleukin 13 (IL-13), and transforming growth factor *β* (FTC*β*).

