### 8.2. Statistical Analysis

For the characterization of the sample, a descriptive analysis of the data will be performed; therefore, the qualitative variables will be described by absolute and relative frequency; the quantitative variables that present normal distribution according to the Shapiro-Wilk test (*p* ≥ 0.05) will be presented as means, standard deviations, and 95% confidence intervals, while those that do not present normal distribution according to the Shapiro-Wilk test (*p* < 0.05) will be presented as medians and respective 95% confidence intervals and 25th and 75% percentiles.

To analyze the quantitative variables between the groups, Student's *t*-test will be used for variables that have a normal distribution and the Mann-Whitney test will be used for variables that do not have a normal distribution.

The confidence level adopted for all analyses will be 95%. All analyses will be performed using the Data Analysis and Statistical Software for Professionals (Stata) version 11.0®.

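### The primary endpoint names a family of proinflammatory cytokines but no single quantity, success rule or multiplicity control; under an any-one-of-six reading a false reduction has a chance of about 14%, against 2.5% for one test

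*Protocol article*

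**What the plan says.** Section 4 (Criteria for Evaluation) gives the whole primary endpoint in one sentence: "The primary endpoint is to analyze the reduction in blood concentration of proinflammatory cytokines". It does not say whether one, all or most of the cytokines must fall, or whether they are to be combined. The abstract repeats this without adding detail. The next sentence of section 4 reads: "The secondary endpoints are to analyze the effect size according to each type of proinflammatory cytokine".

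The size of the family differs between two places:
- Section 7.1 separates the two forms of IL-1 and so lists six: "interleukin 7 (IL-7), interleukin 6 (IL-6), interleukin 2 (IL-2), interleukin 1 (IL-1b and IL-1*α*), and TNF alpha (TNF-*α".
- The abstract (Methods) counts IL-1 once and so lists five: "Proinflammatory (IL-1, IL-2, IL-6, IL-7, and TNF-*α".

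On analysis, section 8.2 works variable by variable: "Student's *t*-test will be used for variables that have a normal distribution and the Mann-Whitney test will be used for variables" without a normal distribution. It closes with one level for everything: "The confidence level adopted for all analyses will be 95"%. It draws no distinction between primary and secondary analyses, states no adjustment, and does not say whether tests are one-sided or two-sided.

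Section 10 (Discussion) gives the primary objective as finding out whether TENS can lower these cytokines. It says that a successful conclusion would identify an anti-inflammatory effect, and it plans to use the results to calculate sample sizes for further trials.

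**The concern.** A primary endpoint should let a reader say, before any data exist, which result would support the hypothesis and which would not. This one does not. The individual cytokines are secondary, so the primary should be something else, perhaps a pooled quantity, but none is defined and section 8.2 describes no way to form one. Either the primary has no variable, or the primary and the first secondary endpoint are the same set of results under two names.

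Two things are at stake:
- **False claim.** With several unadjusted tests and no success rule, the decision about what counts as success can be made after the results are seen.
- **Later trials.** If the cytokine with the largest drop is carried forward into a sample size calculation, its effect is selected as the largest of several and will tend to be too large. The later trial would then be too small.

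**Working it through.** **Inputs from the article**
- Six proinflammatory cytokines (section 7.1) or five (abstract).
- 95% confidence for every analysis, so 0.05 per test, with no adjustment and sidedness not stated (section 8.2).
- 59 patients, single arm, paired analysis (sections 3 and 8.1).

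**Assumptions added here**
- Any one significant reduction counts as success.
- Each test is a correctly specified paired test that holds its nominal level.
- TENS has no effect on any of the cytokines.
- Where a correlation between test statistics is used, it is common to all pairs and equal to 0.3, 0.5 or 0.7.

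**Step 1. The article's own figure.** Section 8.1 takes 59 from a pilot-study formula with 5% probability and 95% confidence: ln(1 − 0.95) / ln(1 − 0.05) = 58.40, rounded up to 59. The figure reproduces. It rests on no effect size, SD or power, so it has no bearing on the error rate. The article states no familywise error rate to reproduce.

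**Step 2. Chance of at least one false reduction, two-sided 5% tests.** Each test has 0.025 in the direction of a reduction.
- Six independent tests: 1 − 0.975^6 = 14.1%. Upper bound under any dependence: 6 × 0.025 = 15%.
- Five independent tests: 1 − 0.975^5 = 11.9%. Upper bound: 5 × 0.025 = 12.5%.
- One test: 2.5%.

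**Step 3. The same with correlated cytokines** (six equicorrelated normal statistics, 1,000,000 simulated draws).

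| Assumed correlation | False reduction, two-sided 5% | Change in either direction, two-sided 5% | False reduction, one-sided 5% |
|---|---|---|---|
| 0 | 14.1% | 26.5% | 26.5% |
| 0.3 | 12.1% | 24.1% | 22.0% |
| 0.5 | 10.4% | 20.7% | 18.6% |
| 0.7 | 8.2% | 16.4% | 14.8% |

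The 26.5% in the first row is 1 − 0.95^6; its bound under any dependence is 6 × 0.05 = 30%. Against 2.5% for one two-sided test, the inflation for a false reduction runs from 14.1 / 2.5 = 5.6-fold under independence to 8.2 / 2.5 = 3.3-fold at correlation 0.7.

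**Step 4. Effect of control.** At 0.05 / 6 = 0.0083 per test, the familywise error is 1 − (1 − 0.0083)^6 = 4.9% under independence and at most 5% under any dependence. For a false reduction it is at most 2.5%.

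**Step 5. Price of control.** Paired t-test, n = 59, 80% power, noncentral t with 58 degrees of freedom:
- alpha 0.05: detectable standardised change 0.371 SD;
- alpha 0.05 / 6: 0.467 SD. Holm never demands more than this, so it is an upper limit.

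**Step 6. Price of a composite.** Suppose one of six cytokines moves by 0.37 SD, the others do not move, and the changes correlate at 0.5. The mean of the six standardised changes shifts by 0.37 / 6 = 0.062. Its SD is √[(1 + 5 × 0.5) / 6] = 0.764. The composite effect is 0.062 / 0.764, or about 0.08 SD.

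**The case against.** **The any-one-of-six rule is not in the text.** This stands. Section 4 makes the per-cytokine effects secondary, which points away from six separate primary tests. The article leaves the primary undefined; it does not set a rule that any single result suffices. The error rates above are therefore conditional on a reading that the wording allows.

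**A reader might infer a 26% chance of falsely claiming a reduction.** The article does not support that figure. It is the chance of a significant change in either direction with six independent two-sided tests. It applies to a false reduction only if each test is one-sided at 5%, and sidedness is not stated.

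**The per-test level depends on the test used.** Section 3 announces a paired analysis, but section 8.2 names a comparison between groups and the Mann-Whitney test, which is for unpaired samples. Unpaired tests on positively correlated before and after values reject too rarely. With an assumed correlation of 0.5, the level is about 0.6% per test and about 3% over six independent tests in either direction. This also stands, which is why the figures here are tied to correctly paired tests.

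**It is a pilot-sized study, and multiplicity details may be in an analysis plan that is not shown.** This holds only in part. Adjustment details may well be elsewhere, and their absence alone would not be a finding. But section 4 sets out to define the primary endpoint and does so without identifying an outcome, with an overlapping secondary and two different counts of the family. The pilot label does not remove the problem either, because section 10 draws a conclusion on whether TENS lowers cytokines and plans to size later trials from the result.

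**Conclusion.** The point holds in a conditional form. As written, the primary endpoint has no single quantity, no success rule and no error control, and the cytokine list itself is unsettled. That much is on the face of the article and rests on no calculation.

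The size rests on the assumptions listed in the working. With six unadjusted, correctly paired, two-sided 5% tests and success on any one, a false reduction has a chance of about 14% under independence and at most 15%. At assumed correlations of 0.3, 0.5 and 0.7 it is about 12%, 10% and 8%. With the abstract's five cytokines the independent figure is 11.9%. The benchmark is 2.5% for one test. These figures cover multiplicity only; they say nothing of bias from a before-and-after comparison without a control group.

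**What to change.** Change the wording of sections 4 and 8.2, before data are seen:

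1. Settle the list of proinflammatory cytokines so that section 7.1 and the abstract agree.
2. Choose one of two routes for the primary endpoint:
   - **Co-primary.** Declare the six cytokines co-primary, each tested on paired data, with Holm adjustment at a two-sided familywise 5%. The cost is a detectable effect of at most about 0.47 SD in place of 0.37 SD with 59 patients and 80% power.
   - **One quantity.** Name one cytokine, or each patient's mean of the standardised log(post/pre) changes, and test it once at two-sided 5%. This keeps 0.37 SD, but for a composite that is in SDs of the composite itself. A composite loses sensitivity if only some cytokines respond (about 0.08 SD in the example above), and its unit is harder to interpret.
3. State that tests are two-sided and what result counts as success.
4. Report the remaining results (individual cytokines where they are not primary, anti-inflammatory cytokines, immunohistochemistry groups) as secondary, with unadjusted confidence intervals labelled descriptive.

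No extra patients, samples or assays are needed unless a larger sample is wanted to recover the power that Holm costs.

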## 5. Subject Selection and Recruitment Strategies

Women diagnosed with breast cancer who meet the inclusion and exclusion criteria will be eligible to participate in this study. The eligibility criteria are described in Table 1.

The study will be carried out on the premises of the clinical research site (Pesquisare Saúde, Santo André, Brazil), and these patients will be recruited as they arrive at the site to be evaluated in the protocols.

Patients are referred to the research site by doctors and partner hospitals who have already been informed of ongoing breast cancer studies. The research criteria have already been passed to all partners, and as soon as a patient is identified, they are invited to go to the research site where all the information is explained in more detail.

## 6. Study Intervention

The consent form will be obtained as the first procedure from all participants by the study coordinator. The confidentiality of the data will be guaranteed until the end of the research.

The study will not be randomized. All patients will be submitted to TENS intervention, and the data will be analyzed in the pre- and postintervention of each patient.

### 6.1. Blinding

Since it is a sensory current, patients will be blinded regarding the modulation of the current (TENS programming values), but not for the sensation and intensity that must be perceived during the application. All of the patients will be asked about the tingling perception that the current causes, and the intensity limit will be the maximum sensation that is tolerated.

The laboratory technicians will be blinded about the study design and will receive the samples identified by number and the indication of pre and post.

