### 7.2. Data Collection and Analysis Methods

The electrodes for applying TENS will be positioned as described previously (Figure 2). After placement, the patient will be accommodated in an armchair where she will remain until the end of the intervention. 8 ml of blood divided into 4 tubes (2 purple tubes of EDTA and 2 yellow tubes of biochemistry) will be collected by peripheral puncture, in the patient's chosen arm. The tubes will be identified as precollection. In order to make the process less invasive, the patient will have venous access until the end of the second collection.

After the end of the 30 minutes of TENS, the same collection process described above will be repeated. The vials will be identified as postcollection.

Blood collection will take place where the TENS intervention will be carried out (Pesquisare Saúde, Santo André). After collection, the samples will be sent on the same day, at room temperature, to the Clinical Analysis Laboratory of the Centro Universitário FMABC (Santo André, Brazil).

Quantitative analysis of serum levels of proinflammatory cytokines will be performed using the enzyme-linked immunosorbent assay (ELISA) technique (BD OptEIA, Biosciences), following the manufacturer's guidelines and adopting the instructions in the manual as a reference value.

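### Laboratory technicians see whether each tube is pre or post, so the cytokine assay is not masked to the only contrast the trial analyses

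*Protocol article*

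**What the plan says.** Section 6.1 (Blinding) states that the laboratory technicians are blinded about the study design and, in the same sentence, that they "will receive the samples identified by number and the indication of pre and post". Section 7.2 applies the labels at collection. For the blood drawn before TENS, "The tubes will be identified as precollection"; for the blood drawn afterwards, "The vials will be identified as postcollection". Samples go to the laboratory on the day of collection, and quantification "will be performed using the enzyme-linked immunosorbent assay (ELISA) technique" following the manufacturer's guidelines.

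Section 3 gives the design: "A nonrandomized, open, single-arm clinical trial with paired analysis will be developed". Section 6 says that all patients receive TENS and that "the data will be analyzed in the pre- and postintervention of each patient". Section 4 defines the outcome: "The primary endpoint is to analyze the reduction in blood concentration of proinflammatory cytokines".

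The article describes no recoding of tubes between collection and assay.

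**The concern.** In a two-arm trial, a visit label on a tube does not reveal treatment. Here it does the equivalent, because every pre sample is untreated and every post sample is treated, and the primary endpoint is the difference between them. The sentence that presents the laboratory as blinded also hands it this information. A number followed by pre or post further suggests a before-and-after comparison, which weakens the stated blinding to the design.

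The practical risk lies where an assay leaves room for judgement: which readings are repeated, how out-of-range values are treated, and where samples sit on a plate. If any of these differs systematically between pre and post samples, the difference enters the primary endpoint directly, and no concurrent control group would show it. Patients know they are being stimulated and the trial is open, so the laboratory is the natural place for effective masking. The Discussion (section 10) plans to use the results for sample-size calculations in later trials, so a measurement bias would carry forward.

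**Working it through.** **Step 1: set the statements side by side.**

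| Question | What the article says | Where |
|---|---|---|
| What are technicians blinded to? | The study design | 6.1 |
| What do they see on each sample? | A number and pre or post | 6.1; labels applied in 7.2 |
| What is compared? | Pre with post, within patient, single arm | 3 and 6 |
| What is the primary endpoint? | Reduction in proinflammatory cytokines | 4 |
| Is time point hidden before assay? | No such step described | 6.1, 7.2 |

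Rows 2 and 3 coincide: the information on the label is the contrast analysed. The measurement is therefore not masked to time point. This conclusion needs no arithmetic.

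**Step 2: the plan's own figure.** Section 8.1 gives 59 participants from a pilot-study method, with 5% probability and 95% confidence. The calculation ln(1 − 0.95) / ln(1 − 0.05) = 58.40, rounded up to 59, reproduces it. The number does not depend on tube labelling and would not change if tubes were coded.

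**Step 3: an illustration of size.** The documents give neither assay variability nor a size for labelling bias, so the inputs below are assumptions:

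- n = 59 pairs (section 8.1).
- No true effect of TENS.
- A constant systematic shift d of 0.05 or 0.10 on the log scale between pre and post readings (assumed; roughly 5% and 10%).
- SD s of the within-patient log change between 0.2 and 0.5 (assumed).
- A paired t-test at two-sided 5%. Section 3 calls the analysis paired; the log scale is chosen here for illustration.

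The noncentrality parameter is (d / s) × √59, with √59 = 7.681. The probability of significance in the direction of the shift is the upper tail of the noncentral t distribution with 58 degrees of freedom beyond the critical value 2.002.

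| s | d = 0.05: noncentrality | Probability | d = 0.10: noncentrality | Probability |
|---|---|---|---|---|
| 0.2 | 1.920 | 47.1% | 3.841 | 96.5% |
| 0.3 | 1.280 | 24.2% | 2.560 | 71.2% |
| 0.4 | 0.960 | 15.5% | 1.920 | 47.1% |
| 0.5 | 0.768 | 11.4% | 1.536 | 32.7% |

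With no shift the figure is 2.5% in each direction. The spread, about 11% to 97%, shows how strongly the result depends on the assumed inputs.

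**Step 4: a second scale.** Express the shift in units of the SD of the paired difference, use the normal approximation and count both directions (nominal 5%). Shifts of 0.05, 0.10, 0.20 and 0.30 SD then give 6.7%, 12.0%, 33.6% and 63.5%. Very small shifts do little harm; moderate ones matter.

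**The case against.** Four points can be made for the plan.

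*The claim is limited to the study design.* The article never says that technicians are blinded to time point. Someone who sees a number with pre or post may still not know what the intervention was or which direction is hoped for, and deliberate directional bias needs a believed direction. This stands. A reader might infer that laboratory blinding is wholly absent, but the text does not support that. What is missing is masking to time point.

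*ELISA is quantitative.* It is run to the manufacturer's guidelines and leaves less room for a reader's expectation than a subjective rating would. This stands and lowers the severity. It does not remove the judgement in repeats, out-of-range values and placement. Nothing in the article says that technicians will use the labels in this way.

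*Plate layout is not stated.* A reader might infer that all pre samples will be run on one plate and all post samples on another, and take the larger figures above as the expected harm. No section describes such a layout, and a condensed article may leave it to a laboratory manual. Both tubes of a patient are collected on one day and could well be run side by side. A plate shift would also arise from layout whether or not anyone is masked, and independent shifts over several plates would partly average out. The figures therefore show sensitivity to a systematic shift of any origin; they do not measure the effect of the labels.

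*Collection staff must know which tube is which.* This is correct, and it shapes the fix: the labels can stay at the site, provided they do not reach the laboratory.

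The general defence that an article condenses a fuller protocol does not answer the core point. The article is not silent here: two sections state how samples are labelled, and 6.1 says what the laboratory receives.

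**Conclusion.** The point holds in a limited form. As written, the cytokine measurement is not masked to time point, the only contrast in this single-arm paired trial, although the passage appears under the heading of blinding. That conclusion rests on sections 3, 4, 6, 6.1 and 7.2 alone. The size of any bias is unknown. The range of about 11% to 97% against a nominal 2.5% rests on an assumed constant log shift of 0.05 to 0.10, an assumed SD of 0.2 to 0.5, 59 pairs and no true effect.

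The severity is that of an inexpensive improvement that reduces one source of measurement bias. It would be too strong to conclude that the labelling invalidates the primary endpoint, because the assay is quantitative and technicians may not know the intervention or the expected direction. Nor would coded tubes allow a pre-to-post change to be attributed to TENS, since the lack of a control arm remains.

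**What to change.** - **Recode before dispatch.** The site may mark tubes pre or post at collection. Before they leave, each tube receives a random code that hides the time point. The study coordinator holds the key until all assay results are final.
- **Assay in pairs.** Send each patient's two samples as a coded pair, and run both on the same plate in random well order. The laboratory can then keep pairs together without knowing which sample came first.
- **Amend the text.** In 6.1, delete the words that give the laboratory the pre/post indication. In 7.2, add the recoding step after collection.
- **If recoding is not adopted,** state in 6.1 that technicians are not masked to time point.

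The cost is a code list and relabelling, with no extra patients or blood. The sample size of 59 is unaffected. The change must be in place before samples are assayed, because masking cannot be restored afterwards.
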